##### Fatty acids composition of total lipids

2.9.7.7.

In conjunction with dietary information collected via the FFQ, circulating proportions of fatty acids in plasma and RBC will be assessed. Total lipids in plasma and RBCs (200 μL) are extracted using the Folch method with a 4:1 ratio (chloroform: methanol (2:1, 8 mL): 0.1 M potassium chloride (KCl, 1.8 mL) (79). Samples are vortexed then incubated overnight at 4°C. Samples are centrifuged at 906 g for 5 min with maximum brake and total lipids (bottom solvent layer) will be dried down under nitrogen gas and resuspended in boron trifluoride: hexane (1:1, 1.5 mL each) to methylate at 110°C for 1 hour. After cooling, 1 mL of ddH2O are added and samples will be incubated overnight at 4°C. Samples are centrifuged at 906 g for 5 min with maximum brake and total lipids (top layer) are dried down to be resuspended in 100 μL hexane for fatty acid methyl esters (FAME) proportional analysis, using an Agilent 8,890 gas chromatograph coupled with an autosampler (7693A) using a 100 m × 0.25 mm × 0.2um CP-Sil 88 fused capillary column for long chain fatty acids. Identification of fatty acids are based on external GLC 502 and GLC 37 standards. The following fatty acids proportion will be determined in the RBC membrane and plasma at baseline and after the intervention period: decanoic/capric (C10:0), undecanoic/undecylic (C11:0), dodecanoic/lauric (C12:0), tridecanoic/ tridecylic (C13:0), tetradecanoic/myristic (C14:0), tetradecenoic/myristoleic (C14:1 n-9), pentadecanoic/pentadecylic (C15:0), hexadecanoic/palmitic (C16:0), hexadecenoic/palmitoleic (C16:1 n-9), (9Z)-hexadec-9-enoic/palmitoleic (C16:1 n-7), heptadecanoic/margaric (C17:0), 10-heptadecenoic (C17:1), octadecanoic/stearic (C18:0), octadecenoic/elaidic (C18:1 T n-9), octadecenoic/oleic (C18:1 n-9), 11-octadecenoic acid/vaccenic (18:1 T n-7), octadecatrienoic /α-linolenic (C18:3 n-3), octadecadienoic/linoleic (C18:2 n-6), eicosanoic/arachidic (C20:0), 11-eicosenoic/gondoic (C20:1 n-9), 11,14-eicosadienoic (C20:2 n-6), 11,14,17-eicosatrienoic/dihomo-γlinolenic acid (C20:3 n-6), eicosatetraenoic/arachidonic (C20:4 n-6), eicosapentaenoic/EPA (C20:5 n-3), tetracosanoic/lignoceric (C24:0), tetracosenoic/nervonic (C24:1 n-9), docosapentaenoic/DPA (C22:5 n-3), docosahexaenoic/DHA (C22:6 n-3).

### Statistical analysis

2.10.

Continuous variables characterizing each study group will be reported as means with standard deviations or medians with interquartile ranges. Categorical variables will be represented as frequencies and proportions. Data will be checked for normality using the Shapiro–Wilk test, and logarithmic transformation will be employed for variables not normally distributed. The main comparisons in this study will be (1) between groups at each time point using analysis of variance with groups as the main effect followed by a multiple-comparison *post hoc* test and (2) within groups using paired *T*-test to assess differences between time points (i.e., baseline vs. post-intervention). Correlation analysis and linear regression models will be performed to verify the associations between outcomes (e.g., immune cell phenotypes and function, and systemic inflammation) and exposure (e.g., dietary intake or metabolic parameters, such as glucose, insulin, HOMA-IR, and HbA1c) variables. Mixed model repeated measures will be used to analyze variables of the OGTT to assess the effects of time, group, and time*group interaction. Overall comparisons of postprandial responses among groups will be determined using the incremental AUC with the trapezoid method. The statistical analyses will be adjusted for potential confounders and their interaction with the main group effect in cases where groups are unbalanced regarding factors such as physical activity level, use of medication (e.g., anti-diabetic drugs), and BMI, sex, and age if groups are not matched as initially planned. Sensitivity analyses will be conducted to verify the effect sizes of the primary outcomes of the study to assess the power and validity of our results. Comparative analyses using pertinent variables (e.g., age, sex, diet, metabolic profile, primary outcomes) will be performed between participants that completed the study with those who did not (i.e., participant dropouts or discontinuers). A *p*-value <0.05 will be considered to be statistically significant. A detailed analysis plan will be developed before the final analysis with a biostatistician.

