### Withdrawal of participants

2.6.

Participants may be withdrawn from the trial either at their own request or at the discretion of the principal investigator if not compliant with the menu. Participants will be made aware via the information sheet and consent form that data collected up to the withdrawal date may still be used in the final analysis. If participants have consumed the control diet for at least 2 weeks, they will be asked if they would like to provide a blood sample before withdrawal. The reason for and date of withdrawal will be recorded on an electronic spreadsheet.

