### Sample size

2.11.

A total of 32 participants per group (*n* = 128) will provide adequate power (β = 0.81, α = 0.05) to assess a mean effect size of 30%, which was calculated based on differences in plasma CRP concentrations and *ex vivo* IL-2 secretion by PHA-stimulated PBMCs between Obese-NG and Obese-T2D participants. The sample size calculation was performed using data from a previous study (43) and the software G*Power. We applied a conservative attrition rate of 30% based on previous controlled feeding studies that ranged from 10–35% (81–85), totaling 166 participants.

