### Adverse event reporting

2.13.

For this study, we followed the reporting requirements of the Health Research Ethics Board Biomedical Panel of the University of Alberta. Adverse events and other unintended effects will be collected weekly throughout the study from a self-monitoring form that participants will be asked to fill out daily. In addition to this method, participants will be advised to contact the study team directly to report any events. Expected events of this study, anticipated in the participants regardless of participation in research, may include unknown food allergies, gastrointestinal symptoms, changes in glycemia, and lipid profile. Although physiological changes may occur during participation in the study due to modifications in dietary patterns, they are not considered an adverse event unless they are unfavourable to the participant. To better understand if events could be related to the study we will evaluate the incident, its duration, and severity of symptoms. If a participant reports an incident of suspected foodborne illness we will investigate it to determine if there are other factors that may have caused it (i.e., improper food handling once food taken from HNRU, other illnesses in the household, food intolerance, etc.). Then we would send the food samples kept on site for testing to confirm if there was the presence of pathogens in the food. Only adverse events that are serious and unanticipated will be reported to the Research Ethics Office electronically through the Alberta Research Information Services (ARISE) System. Care will be provided to participants that suffer intervention-related harms. Participants will be instructed to seek medical attention and will be removed from the study if they are unable to comply with the feeding protocol due to acute illnesses not related to the study that may arise. If participants are willing to continue the feeding protocol after an acute illness (e.g., a cold), they will be asked to remain another week in the study to have their final appointments.

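### The post-diet analyses of CRP and IL-2 use only participants with a post-intervention value, so the baselines of non-completers are wasted and selective dropout goes uncorrected

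*Protocol article*

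**What the plan says.** Section 2.10 of the protocol article names two main comparisons. One is "between groups at each time point using analysis of variance with groups as the main effect", followed by a post hoc test. The other is "within groups using paired *T*-test to assess differences between time points (i.e., baseline vs. post-intervention"). The only longitudinal model is kept for a different purpose: "Mixed model repeated measures will be used to analyze variables of the OGTT". The same section plans a comparison of participants who finish with those who do not, sensitivity analyses of the primary-outcome effect sizes, and a detailed analysis plan to follow.

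On loss, section 2.11 states: "We applied a conservative attrition rate of 30% based on previous controlled feeding studies" (range 10% to 35%), "totaling 166 participants". Participants can leave at their own request or for menu non-compliance (2.6), through exclusion below 90% compliance (2.9.1), or because of illness: they "will be removed from the study if they are unable to comply with the feeding protocol due to acute illnesses" (2.13).

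On the data of those who leave, section 2.6 says that "data collected up to the withdrawal date may still be used in the final analysis". It also says that anyone with at least 2 weeks on the diet will be asked for a blood sample before leaving. The article does not say which analysis would use these data, or whether that sample stands in for the post-intervention value.

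**The concern.** A post-intervention ANOVA and a paired t-test each need a post-intervention value. A participant who has a baseline CRP or IL-2 but no later sample contributes nothing to either, even though the baseline carries information about the missing value. The mixed model that would use it is assigned to the OGTT variables, not to the primary outcomes.

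The first objective concerns obesity and glycemia independently of diet, so the contrast after the common diet is the one that bears on it, and it is the one exposed to loss. Some exits could plausibly relate to group and to inflammation: the introduction itself says that obesity and type 2 diabetes raise infection risk, and acute illness is a ground for removal. At stake are some precision in any case, and bias if dropout is selective to a different degree in different groups.

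**Working it through.** **Plan's own figures.** A one-way ANOVA with 4 groups, N = 128, alpha 0.05 and effect size f = 0.30 (my reading of the 30%) has power 0.810, matching the stated 0.81. The enrolment figure follows from 128 × 1.30 = 166.4, stated as 166.

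**Who is left after the diet.** 166 × 0.70 = 116, or about 29 per group, if the full 30% is lost and no early-withdrawal sample is used. About 166 − 116 = 50 enrolled participants would then have no post-diet value. ANOVA power at N = 116 and f = 0.30 is 0.765. Whether 166 is the right inflation is a separate matter.

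**Assumptions, not in the documents.** 41 enrolled per group (166/4 = 41.5), outcome SD 1 at both times, baseline-to-final correlation ρ of 0.5 to 0.8, dropout fraction d = 0.30, and a true difference of 0.60 SD between two groups.

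**Precision with non-selective dropout.** The completer contrast has SE = √(2/(41 × 0.7)) = 0.264. Using all baselines multiplies the variance by about 1 − dρ².

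| ρ | √(1 − 0.3ρ²) | Completer SE relative to all-baseline SE |
|---|---|---|
| 0.5 | 0.962 | 1.04 |
| 0.7 | 0.924 | 1.08 |
| 0.8 | 0.899 | 1.11 |

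Simulation agrees. The completer SE is about 0.265, against 0.257 (ρ = 0.5), 0.246 (ρ = 0.7) and 0.239 (ρ = 0.8). The ratios are 0.265/0.257 = 1.03, 0.265/0.246 = 1.08 and 0.265/0.239 = 1.11. At ρ = 0.7 the variance falls by 1 − (0.246/0.265)² = 14%. For the within-group change the gain is smaller: the variance factor (1 − ρ²) + (1 − ρ)² becomes (1 − ρ²) + 0.7(1 − ρ)². At ρ = 0.7 that is 0.600 against 0.573, about 2% in SE.

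**Bias with selective dropout in one group.** Let the dropout logit be log(0.3/0.7) + slope × baseline in one group, with a constant 30% in the other. Completers' mean baseline then shifts by −(dropout fraction) × (gap between dropouts and completers):

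- slope 0.5: −0.310 × 0.475 = −0.147 SD
- slope 1.0: −0.331 × 0.838 = −0.277 SD

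The bias in the week-4 contrast is ρ × shift.

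| ρ | slope 0 | slope 0.5 | slope 1.0 |
|---|---|---|---|
| 0.5 | 0 | −0.07 | −0.14 |
| 0.7 | 0 | −0.10 | −0.19 |
| 0.8 | 0 | −0.12 | −0.22 |

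In simulation at ρ = 0.7, the completer estimates of the true 0.60 are 0.59, 0.50 and 0.41 for slopes 0, 0.5 and 1.0; the all-baseline estimates are 0.59, 0.60 and 0.61. Within the selected group, the paired change is biased by (ρ − 1) × shift. At ρ = 0.7 that is −0.3 × −0.147 = +0.04 and −0.3 × −0.277 = +0.08 SD.

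**The case against.** The strongest reply is that an article may leave analysis sets and missing-data handling to the later plan, and section 2.10 announces one. That holds for missing detail. Here, however, the article fixes the method for the main comparisons and assigns the mixed model elsewhere, so the later plan would have to replace what is stated.

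Second, the size is assumed. No document gives the correlation or the dropout mechanism, the largest bias shown is under one SE (0.22/0.265 = 0.83), and without selection there is none. The simulated dropout depends on baseline alone, which is exactly the case that the mixed model repairs. All of this stands. Dropout driven by events during the diet, such as acute illness, may not be repaired.

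Third, the risk is partly addressed. The completer comparison can reveal selection, some leavers may give a sample under 2.6, and under 2.13 participants willing to continue after an acute illness stay another week for their final visits. These provisions reduce or describe the loss; they do not correct for it.

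A reader might also infer more than the text supports:

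- That every stated analysis drops participants without a final sample. The baseline ANOVA needs none.
- That the two ANOVAs cover different people. The article does not say whether the baseline ANOVA uses all enrolled or completers only.
- That 30% will leave before the final sample. It is a planning allowance described as conservative.
- That a shift in the group difference from baseline to week 4 would mix diet with dropout. No planned analysis compares the two ANOVAs, and change is tested in the same people by the paired t-test.

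**Conclusion.** The point holds in limited form. For the primary outcomes, the two post-diet analyses in section 2.10 leave the baselines of non-completers unused, while the protocol plans for substantial attrition and already intends to use a suitable model for other variables. At 30% loss, the cost for a week-4 contrast is an SE about 3% to 11% too large for correlations of 0.5 to 0.8. Bias is conditional: about 0.07 to 0.22 SD if dropout in one group depends on baseline at log-odds of 0.5 to 1.0 per SD, and nil if dropout is unrelated to outcome. The documents do not establish that dropout will be selective, so this is a design weakness worth repairing, not a demonstrated bias.

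**What to change.** In section 2.10 or the analysis plan:

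1. For log CRP and log IL-2, replace the post-intervention ANOVA and the paired t-tests with one mixed model on all participants with a baseline value. Include group, time and group × time, with an unstructured within-person covariance. Take the week-4 group contrasts and the within-group changes from it.
2. Keep the completer-only analysis as a sensitivity analysis.
3. State whether the early-withdrawal sample in section 2.6 counts as the post-intervention value.

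This costs wording only: the baselines are already collected and mixed models are already planned for the OGTT. The downside is the assumption that dropout is missing at random given baseline and group, so bias from dropout driven by later events would remain. The completer versus non-completer comparison should stay, as a description of who was lost.

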### Study objectives and hypothesis

2.1.

The study objectives are:

To establish the independent contribution of obesity and glycemia, independent of diet, on systemic inflammation and immune function outcomes. We hypothesize that systemic inflammation will increase and T cell function, characterized by *ex vivo* IL-2 secretion upon phytohemagglutinin (PHA) stimulation, will decrease progressively from the Lean-NG to Obese-T2D group.To determine the role of glycemia on postprandial inflammatory and immune responses using an OGTT. We hypothesize that a higher glucose AUC will be associated with increased inflammatory responses, a higher proportion of activation markers expressed on immune cells, and a lower proliferation rate by PBMC upon stimulation with anti-CD3/CD28 in Lean-NG, Obese-NG, Obese-GI, and Obese-T2D individuals.To explore the relationship between diet, metabolism, and immune function. We hypothesize that a higher habitual consumption of DHA and choline and lower consumption of SFA, will be associated with enhanced immune function and lower levels of systemic inflammation. Specifically, a higher proportion of DHA in the membranes of RBC will be associated with improved Th1 response (i.e., IFN-γ and TNF-α), despite similar production of IL-2 upon immune challenge, whereas systemic inflammatory markers will be lower. Higher consumption of choline in the form of phosphatidylcholine will improve IL-2 production upon T cell stimulation. Other dietary components (e.g., fiber, antioxidants, and vitamins) will be associated with enhanced immune function in individuals with and without obesity with varying levels of glycemia.

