### Study design

2.3.

The NutrIMM study is a prospective, non-randomized, four-arm, parallel-group, unicentre, controlled-feeding trial conducted at the Human Nutrition Research Unit (HNRU), University of Alberta (Edmonton, AB, Canada). A total of one-hundred and twenty-eight participants aged between 18 and 70 years will be assigned with a 1:1 male to female ratio to one of four groups (*n* = 32 per group): Lean-NG, Obese-NG, Obese-GI, Obese-T2D. All participants will be followed up for a total of 4 weeks from the date of group allocation. It will not be possible to blind participants or researchers due to the inclusion specifications of the groups. An overview of the study design is shown in Figure 1.

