## Discussion

3.

Obesity and T2D are associated with an increased risk of infections and a worse prognosis. Immune dysfunction in these conditions may be caused by abnormalities such as excess visceral adiposity (86), hyperglycemia (87), and unhealthy dietary habits (88). However, there is a lack of clinical trials that have controlled for diet and investigated immune function outcomes in males and females with obesity across different metabolic phenotypes.

To address this gap, the NutrIMM study aims to identify immune markers that are impaired in different health conditions, independent of the effect of diet. This study will also explore the relationship between dietary components, biological sex, and immune function. By understanding these differences, we hope to identify targeted and personalized approaches to improve immunity based on sex and metabolic phenotype.

Our investigation may also lead to the identification of circulating inflammatory markers that predict a lower immune function in individuals with obesity and T2D. This is important for diagnostic purposes as common techniques used to assess immune function are not practical for routine diagnosis. Moreover, our study may identify key nutrients that could improve immune function and guide future targeted and personalized interventions for subsequent trials.

The NutrIMM study is the first to determine the independent contribution of diet, sex, excess body fat, and altered glucose levels on inflammation and immune dysfunction associated with obesity. Other strengths of our protocol include assessing immune function outcomes under controlled feeding conditions, which provides valuable information about the effects of different foods, nutrients, and dietary patterns on health outcomes. This type of study allows for careful monitoring and manipulation of food intake, direct measures of physiological responses to different foods and nutrients, and the development of personalized nutrition recommendations based on an individual’s unique physiological response (89–91).

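### Sex is a balanced design factor but enters the between-group models only if matching fails, so a matched trial runs a mildly conservative group test and has no named analysis behind the Discussion's claim about sex

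*Protocol article*

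**What the plan says.** **Design.** Under Study design, the 128 participants "will be assigned with a 1:1 male to female ratio to one of four groups", with 32 per group. Under Recruitment, participants are to be matched by age and sex, but only where this can be done.

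**Analysis.** Under Statistical analysis, the main between-group comparison at each time point is made "using analysis of variance with groups as the main effect followed by a multiple-comparison" post hoc test. A later sentence in that section adjusts for potential confounders, and for their interaction with group, where groups are unbalanced. The list covers physical activity, medication use "and BMI, sex, and age if groups are not matched as initially planned". The regression exposures given as examples are dietary and metabolic, and the OGTT mixed model lists time, group and their interaction. The only other use of sex in the section is the comparison of completers with non-completers. A detailed analysis plan is deferred.

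**Claims.** The first objective is "To establish the independent contribution of obesity and glycemia, independent of diet, on systemic inflammation and immune function outcomes", and none of the three objectives mentions sex. The Discussion says "This study will also explore the relationship between dietary components, biological sex, and immune function" and hopes to "identify targeted and personalized approaches to improve immunity based on sex and metabolic phenotype". It then states: "The NutrIMM study is the first to determine the independent contribution of diet, sex, excess body fat, and altered glucose levels".

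**The concern.** Balancing a factor by design and then leaving it out of the model when the balance is achieved is the wrong way round. Balance removes confounding by sex. It does not remove the variance due to sex from the residual; only a sex term in the model does that. The rule also means that the sex effect and the sex-by-group interaction are fitted when recruitment misses its target and not when it meets it.

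Two things are at stake. The first is some precision in the group comparisons of CRP and IL-2, which the 1:1 design makes available at almost no cost. The second is the standing of anything later said about sex: the Discussion promises more than the described analyses would deliver in a successfully matched trial.

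**Working it through.** **1. Reproduce the plan's own figure.** Inputs from Sample size: 4 groups of 32 (N = 128), α = 0.05, power 0.81 (printed as β), effect size given as 30%. Taking the effect as Cohen's f = 0.30 in a one-way ANOVA:
- noncentrality λ = N f² = 128 × 0.09 = 11.52, with 3 and 124 degrees of freedom
- power = 0.810, matching the stated 0.81

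Reading the 30% as a two-group standardized difference of 0.30 with 32 per group gives only 0.22. The stated power therefore fits a four-group model without sex. That f = 0.30 was intended is inferred from this match; the article does not say so.

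**2. Set up the comparison.** Assume exact balance, 16 men and 16 women per group. Let r be the share of within-group variance due to sex. The article gives no value, so r is an assumption. Total within-group variance is held fixed.
- *Sex in the model:* the residual variance falls by the factor (1 − r), so f becomes 0.30/√(1 − r), with 3 and 123 degrees of freedom.
- *Sex left out:* group means are unaffected by sex because every group has the same mix, so there is no bias. The residual sum of squares, however, contains the sex component. Over the true error variance it follows a noncentral χ² with 124 degrees of freedom and noncentrality 128r/(1 − r). The denominator is too large, so the F ratio is too small.

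**3. Results.**

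| Assumed sex share r | Size of nominal 5% group test, sex left out | Power, sex left out | Power, sex included |
|---|---|---|---|
| 2% | about 0.047 | 0.81 | 0.819 |
| 5% | about 0.041 | 0.81 | 0.832 |
| 10% | about 0.033 | 0.81 | 0.853 |
| 20% | about 0.021 | 0.81 | 0.895 |

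The sizes come from simulation. Numerical integration of the distribution in step 2 gives 0.0465, 0.0416, 0.0338 and 0.0206, which agrees within simulation error. By the same integration, power without sex is 0.811, 0.811, 0.812 and 0.815. The power forgone is therefore about 1, 2, 4 and 8 points.

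**4. Cost of including sex if it has no effect.** Power is 0.8101 with the main effect and 0.8097 with the interaction as well, against 0.8102 without sex.

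**5. What the design can say about sex.** For a sex main effect (64 v 64), power is 0.39, 0.61 and 0.80 at assumed standardized differences of 0.3, 0.4 and 0.5. For the 3-degree-of-freedom sex-by-group interaction, it is 0.13, 0.26 and 0.44 at assumed f = 0.10, 0.15 and 0.20. The design can detect a moderate main effect, but it is weak for interactions of modest size.

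**6. Text against text.** With matching achieved, the named outcome analyses are the group ANOVA, the within-group paired t tests, the correlations and regressions on exposures (dietary and metabolic in the examples given), and the OGTT models. None has a sex term. The Discussion sentence on independent contributions lists sex alongside diet, body fat and glucose.

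**The case against.** The strongest reply has four parts.

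- **Sex is not an objective.** It appears in none of the three objectives and in neither primary outcome, and the Discussion also uses the more modest verb, explore. This stands. A reader might infer that the trial has promised a sex objective and would leave it unexamined; the article does not support that. The mismatch lies in one Discussion sentence.
- **Sex could still be analysed.** The conditional sentence concerns confounder adjustment and does not forbid other uses of sex. The regression exposures are only examples, and a detailed plan is to follow. This stands too, so the point cannot be that sex will go unanalysed. It does not remove the conditional rule, which is fixed in the article and is what the point addresses.
- **The group test is sound.** A reader might infer that omitting sex biases the group contrasts, inflates error or leaves the trial underpowered. It does none of these: under balance the contrasts are unbiased, the test errs on the safe side, and power stays at about the planned level. The loss is a gain not taken.
- **The size rests on assumptions.** The article supports no particular sex share, and exact 16/16 cells are an inference from a 1:1 ratio combined with matching only where feasible. This is correct, which is why the 2% to 10% range leads here rather than the 20% row.

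The article plans no separate analyses in men and women, so a warning about misreading such results would be aimed at something it does not propose.

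**Conclusion.** The point holds in a limited form. The rule that admits sex only when matching fails is a poor choice for a factor balanced by design. With matching achieved, the nominal 5% group test runs at about 0.047, 0.041 or 0.033 and forgoes about 1, 2 or 4 points of power, for assumed sex shares of 2%, 5% or 10%. These figures rest on f = 0.30 (inferred from the stated power), exact balance within groups, and the assumed shares. If sex explains little of the variance, the loss is negligible.

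Separately, the Discussion's claim to determine the contribution of sex outruns the analyses named, and it sits uneasily with the article's own exploratory wording and its objectives. Neither matter undermines the primary comparisons.

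**What to change.** - **Statistical analysis (2.10):** include sex as a fixed factor in every between-group model of CRP and IL-2, whether or not matching succeeds, and take it out of the conditional list.
- **Same section:** report the sex effect and one sex-by-group interaction test per primary outcome, each with 95% confidence intervals and labelled exploratory. The interaction power in step 5 supports that label.
- **Discussion:** for sex, replace the verb determine with explore, in line with the earlier sentence there.

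The deferred analysis plan can carry the first two changes. No new data are needed, since sex is already recorded and balanced by design. The cost is one degree of freedom for the main effect, three more where the interaction is fitted (power 0.8097 rather than 0.8102 if sex has no effect at all), and a more modest claim about sex.
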